### Intervention

The intervention consists of seven sessions: Goal setting and motivational interviewing (session 1), impulse control (session 2), problem solving (session 3), cognitive restructuring (session 4), self-worth (session 5), relapse prevention (session 6), and a booster session 4 weeks after completion of the core sessions (session 7) (see Table 1 for an overview of the main sessions). Moreover, participants can choose between several elective sessions based on individual need and preference. The elective sessions are directed at personal needs and values, sleep, relaxation, alcohol and affect regulation, appreciation and gratefulness, and procrastination (see Table 2 for an overview of the elective sessions). Each session can be completed in ~30–45 min. We advise participants to do at least one and a maximum of two sessions per week. Further content can only be accessed once previous sessions are completed. Consequently, the training will last about 4–6 weeks plus one additional booster session 4 weeks after completion of the last session. The booster session aims to help participants to refresh and reflect contents and strategies. Sessions consist of texts, testimonials, and include many interactive elements such as quizzes, exercises, and homework, which can be seen in the Supplementary Material. At the end of the second session, a plan for behavior change is introduced. This four-step plan aims to help participants to (1) choose specific situations in which they want to change their internet use, (2) set realistic goals, (3) collect ideas on how to realize their goals, and (4) to create a detailed plan for goal acquisition including newly acquired strategies and planning for potential upcoming difficulties. Participants are expected to test their plan for behavior change during the following week and are encouraged to analyze success and difficulties in the training process in the next session. They can also opt to review and adapt their plan in the following session. Participants are encouraged to formulate five plans in total over the course of the training between the second and the sixth session. They are also invited to keep an online diary, which can be accessed via the web interface or an optional smartphone app. The intervention uses content tailoring, thereby engaging the participants by encouraging them to make real-time choices among various response options, and then providing individualized content based on specific needs or preferences. The training is built on responsive web-design and can be completed on any kind on internet-ready device, such as PCs/laptops, smartphones, or tablets. Participants can also opt to receive motivational messages and small exercises referred to as *Tiny Tasks*. These smartphone notifications are sent directly to their mobile device 3 times a day. These notifications will support the participants in transferring the exercises of the training into their daily lives (e.g., giving suggestions on how to implement strategies: “What has influenced your internet usage today?”).

**Table 1 T1:** Content of the training.

**Intervention content**	**Session**
Goal setting and motivational interviewing	1
Impulse control	2
Problem solving	3
Cognitive restructuring	4
Self-worth	5
Relapse prevention	6
Booster session	7

**Table 2 T2:** Content of the elective sessions.

**Session**	**Content**
Relaxation	Learning the progressive muscle relaxation to reduce tension
Alcohol & affect regulation	Reducing affect regulation related alcohol consumption
Personal needs & values	Reducing personal incongruence in daily life, by achieving balance between personal needs and values
Appreciation & gratefulness	Focusing on the good things and practicing mindfulness strategies
Sleep	Improving sleep hygiene and practicing sleep restriction to enhance sleep quality
Procrastination	Practicing strategies addressing delaying important tasks

#### Goal Setting and Motivational Interviewing (Session 1)

The first session gives an overview of internet usage in everyday life (e.g., social media, news, online dating), the upcoming sessions, and basic techniques of the intervention. To support participants, three fictional patients are introduced who vary in age, gender and ethnicity, being addicted to online gaming, social media or online dating. One of the main elements of the first session is psychoeducation on the subject of IUD, including the difference between common and problematic internet use, and epidemiology of the disease. Based on that, elements of the motivational interviewing are implemented such as elaborating on personal advantages and disadvantages of using the internet, individual motivation for and confidence in behavior change. Finally, participants are encouraged to create a precise treatment goal using the SMART model.

#### Impulse Control (Session 2)

The second session introduces the concept of impulse control and self-control in order to help the participants to handle feelings of craving to go online in everyday life. Participants can choose between different exercises, each of them illustrating one strategy [(1) distraction, (2) positive self-instruction, (3) social support, (4) awareness of consequences, (5) stimulus control, (6) mindfulness, and consciousness of the presence]. Afterwards, participants are invited to learn about the benefit of their individual resources (e.g., physically, psychologically, socially) regarding coping of daily hazzles or crisis and implementation of strategies. Finally, they are presented with a list of positive activities offering alternatives to the internet and can create a detailed plan when and where to implement the activities.

#### Problem Solving (Session 3)

In the third session, participants are presented with strategies on how to deal with difficulties to stay offline. These strategies address motivational problems, fear of missing out on social situations online, problems in accepting oneself in real life, and loosing social integration online. To enhance their understanding of their problems, participants are introduced to the TRIAS disorder model (25). Based on the TRIAS-Modell participants can then identify individual influencing factors on their internet usage such as their environment (e.g., family, challenging conflict situations), personal dispositions and characteristics (e.g., personality, coping strategies), opportunities of the internet (e.g., self-representation, social contacts) and develop specific strategies such as positive self-instructions with the help of their impulse control and self-control techniques. Participants then learn about psychological, physical, and social maintaining factors of the disorder in combination with specific coping techniques such as strengthening their self and their social relationships offline.

#### Cognitive Restructuring (Session 4)

In the fourth session, participants are introduced to cognitive restructuring, receiving information on the causal relationship between cognitions, emotions, behavior, and consequences. Participants can then individualize their personal thought records by including personal situations, cognitions, and emotions. After psychoeducation about negative emotions and acceptance, participants create positive and helpful thoughts to contrast their negative thoughts in their thought record. To generally concentrate on and practice positive thinking habits, strategies as taking notes or using cues to remind themselves of helpful thoughts and imagining, how helpful thought would alter the current situation.

#### Self-Worth (Session 5)

This session aims at highlighting the importance of self-confidence, self-worth and self-efficacy concerning meeting challenges and controlling internet usage. First, participants learn how their internet use can affect their self-worth and vice versa. To strengthen their self-worth, participants are initially invited to state their positive characteristics and skills. After that, the concept of the inner critic, representing self-doubting cognitions, and the benevolent companion, representing self-conductive cognitions, are introduced and participants are encouraged to identify their own self-doubting and negative self-deprecating cognitions, and confront them with their benevolent companion. Lastly, participants plan the upcoming days with activities that foster self-care, such as spending time with friends and family or pursue hobbies.

#### Relapse Prevention (Session 6)

In the last session, participants can review brief summaries of each session. They are asked to reflect on their progress concerning their intervention goals, and to identify mechanisms of their individual behavior change during the intervention as well as helpful psychological strategies. Subsequently, they are encouraged to make a specific plan of strategies they want to continue exercise in everyday life until the booster session, in order to maintain and generalize acquired strategies.

#### Booster Session (Session 7)

The participants are invited to complete a booster session 4 weeks after completion of the sixth session. In this session, they can reflect on their learning experience and personal goal attainment. They are asked to consider their current use of the internet, and are provided with additional information on support, if needed. Participants can review the letter they wrote to themselves and set new goals for the upcoming months.

#### Guidance

During the active intervention phase, participants of the treatment arm receive content-focused guidance (26) by an eCoach who provides individual manualized feedback after completion of each session. eCoaches will have at least a Bachelor's degree in Psychology and have access to supervision when required. Guidance is based on a treatment manual with preformulated standardized text blocks that are prepared for every lesson and individually adapted for participants according to their input and overall progress. As an additional feature, participants have the chance to contact their eCoach through the internal messaging function of the platform. Estimated mean time per feedback is 30 min. eCoaches are advised not to use more than 40 min per individual feedback. Approximately 2.5 h is the total time an eCoach will spend per participant. Session adherence is also monitored, when participants do not complete a session within 7 days, eCoaches will send out email reminders after 7, 14, and 21 days. Additionally, after 28 days a reminder will be sent via text message. Reminders have shown to improve adherence to self-guided behavior change interventions (27, 28). All study participants can contact a support email address in case of any technical difficulties regarding the intervention.

### Assessment and Data Management

Self-reports will take place at screening (T0), baseline (T1) prior to randomization, post-intervention (T2) 7 weeks after randomization, at 6- (T3) and 12-month follow-ups (T4; see Figure 1 for a detailed overview). Self-reported data will be collected using a secure online-based assessment system (AES, 256-bit encrypted).

### Outcomes

#### Primary Outcome

In order to assess the effect of the treatment on symptoms of IUD, the Internet Addiction Test [IAT; (7)] is administered. The IAT is a widely accepted and validated testing instrument that examines a variety of symptoms of internet dependency (29). The 20 items assess, on a 5-point Likert Scale (1 = “rarely,” 2 = “occasionally,” 3 = “frequently,” 4 = “often,” 5 = “always”) the participant's preoccupation with the internet (e.g., “How often do you block out disturbing thoughts about your life with soothing thoughts of the internet?”), excessive use (e.g., “How often do you lose sleep due to late-night logins?”), neglection of work and social life (e.g., “How often does your job performance or productivity suffer because of the internet?”, “How often do you form new relationships with fellow on-line users?”), anticipation (e.g., “How often do you find yourself anticipating when you will go online again?”), and loss of control (e.g., “How often do you try to cut down the amount of time you spend on-line and fail?”). In several studies, the scale has been shown very good internal consistencies (α = 0.91, α = 0.89) (30).

#### Secondary Outcomes

##### Compulsive internet use

The Compulsive Internet Use Scale (CIUS) (31) consists of 14 items, which refer particularly to the compulsive and impulse control elements of internet use, assessing the severity of symptoms on a 5-point Likert Scale. In several studies, the CIUS has proven to be a valid instrument and has shown good internal consistency (α = 0.89) (32). The scales include withdrawal symptoms, loss of control, preoccupation/salience, conflict (referring to social and work life) and coping (using the internet to cope with stressors).

##### Depressive symptoms

Self-reported depressive symptoms will be measured with the Patient Health Questionnaire (PHQ-9) (33). This frequently used self-report instrument consists of 9 items that are answered on a 4-point Likert scale referring to the previous 2 weeks. Total scores range from 0 to 27. The internal consistency of this measure has been found to be excellent (α = 0.83–0.92) (34).

##### Anxiety

The generalized anxiety disorder measurement (GAD-7) is used to assess symptom severity (35). It consists of 7 items answered from 0 (not at all) to 3 (nearly every day). It possesses excellent internal consistency (α = 0.92) and good test-retest reliability (Intraclass Correlation Coefficient = 0.83) (35, 36).

##### Problematic alcohol consumption

We will use the 3-item version of the Alcohol Use Disorder Identification Test (AUDIT-C) to measure problematic alcohol consumption of the participants on a 5-point Likert Scale (37). The AUDIT-C is a validated and widely used brief screening test for heavy drinking, alcohol abuse, or dependency (38). Even though the internal consistency is only satisfactory (α = 0.77–0.80), it is outweighed by the brevity of the AUDIT-C (39).

##### Insomnia

Insomnia severity will be assessed by the Insomnia Severity Index (ISI) (40), consisting of 7 items to be answered on a 5-point Likert scale. Psychometric properties have been shown to be good (α = 0.83) (41).

##### Worries

In order to evaluate worries, the ultra-brief version of the Penn State Worry Questionnaire (PSWQ-3) (42) is applied. It is a questionnaire that assesses self-reported key aspects of worry, consisting of three items, which are rated on a 5-point Likert Scale. Cronbach's alpha has shown to be 0.74 (43).

##### Procrastination

The 9-item-version of the General Procrastination Scale (GSP-K) is administered to measure procrastination behavior on a 4-point Likert Scale (44, 45). Overall, the questionnaire shows a very good internal consistency (α = 0.92).

##### Gambling

The German questionnaire Kurzfragebogen zum Glücksspielverhalten (KFG) (46) addresses lifetime gambling behavior and consists of 20 items, each on a 4-point Likert Scale. The threshold for pathological gambling is set at 16 points. The questionnaire shows a satisfactory internal consistency (α = 0.79) (47).

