Treating IUD via the internet may appear contradictive at first. However, there are many arguments supporting this approach: (1) Reaching the target group through their common online setting could be effective as the internet is easily accessible and attractive. (2) Since the target group usually shows low levels of treatment motivation (19), an easily accessible and attractive treatment option is crucial; thus, a low-threshold intervention with interactive audio-visual content may facilitate access and reduce burdens of help-seeking. (3) Due to the individually tailored and adaptable content, a variety of symptoms associated with IUD such as procrastination, bad sleep patterns or alcohol consumption can be addressed. Based on these comorbid symptoms, secondary outcome measures were chosen to assess a reduction in symptoms associated with IUD that were targeted in the intervention. (4) Internet- and mobile-based interventions might be a feasible means to provide evidence-based treatment on a large-scale basis, since they have been shown to be effective in the treatment of numerous mental health disorders (20–23). Therefore, internet- and mobile-based interventions could be a way to reach individuals with IUD better than traditional approach. To the best of our knowledge, this is the first trial evaluating a guided internet- and mobile based intervention for IUD in an RCT design.

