#### Other Assessments

Other assessments include demographics (e.g., age, gender, occupation, level of education) and current and previous experience with psychotherapy, self-esteem via Rosenberg Self-Esteem Scale (RSES) (71) and social phobia via Mini Social Phobia Inventory (Mini-SPIN) (72). For an overview of all outcome measures, see Table 3.

**Table 3 T3:** Overview study self-report assessments.

**Construct**	**Questionnaire**	**T1**	**T2**	**T3**	**T4**
Demographics	Socio-Demographic Data	✓	–	–	–
Internet addiction	Internet Addiction Test (IAT)	✓	✓	✓	✓
	Compulsive Internet Use Scale (CIUS)	✓	✓	✓	✓
Depression	Patient Health Questionnaire (PHQ-9)	✓	✓	✓	✓
Anxiety	General Anxiety Disorder Measurement (GAD-7)	✓	✓	✓	✓
Alcohol abuse	The Alcohol Use Disorders Identification Test (AUDIT-C)	✓	✓	✓	✓
Sleep	Insomnia Severity Index (ISI)	✓	✓	✓	✓
Worries	Penn State Worry Questionnaire – Ultra Brief Version (PSWQ-3)	✓	✓	✓	✓
Self-esteem	Rosenberg Self Esteem Scale (RSES)	✓	–	–	–
Social phobia	Social Phobia Inventory (Mini-SPIN)	✓	–	–	–
Procrastination	General Procrastination Scale—Short Version (GPS-K)	✓	✓	✓	✓
Gambling	Kurzfragebogen zum Glücksspielverhalten (KFG)	✓	✓	✓	✓
Wellbeing	WHO-5 Wellbeing Index (WHO-5)	✓	✓	✓	✓
Quality of life	Assessment Quality of Life (AQoL-8D)	✓	✓	✓	✓
Work limitations	Work Limitations Questionnaire (WLQ)	✓	✓	✓	✓
Health economic evaluation	Trimbos Questionnaire for Costs Associated with Psychiatric Illness (TiC-P)	✓	–	✓	✓
Training and acceptability	Client Satisfaction Questionnaire (CSQ-8)	–	✓	–	–

*T1, baseline; T2, post-intervention; T3, 6-month follow-up; T4, 12-month follow-up*.

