### Statistical Methods

Data will be analyzed on an intention-to-treat basis including all participants who will be randomly assigned to conditions. Additionally, study completer analyses including only participants who filled out the questionnaires and intervention completer analyses including only participants who have completed at least four out of six sessions will be conducted. Missing data will be handled using multiple imputations (MIs) calculated by a Markov Chain Monte Carlo multivariate imputation algorithm of 100 estimations per missing value. MI is especially robust with respect to missing data. We will conduct an ANCOVA to examine differences in the primary outcome. To detect differences between the two study groups, we will conduct univariate analysis of covariance to compare secondary outcomes at post-treatment and 6- and 12-month follow-up adjusting for baseline scores. Predictors and mediators of changes of the primary outcome will be analyzed on exploratory basis using linear regression. For all analyses on continuous measures, Cohen's d (74) will be calculated by standardizing the differences between baseline and follow-up scores by the pooled standard deviation of the baselines scores.

The response rates will be compared across conditions with the help of contingency tables and Chi-Squared tests. For primary analysis, significance levels will be set at 0.05, one-sided. For the explorative analysis of the data, the significance levels will be set to 5%. All analyses will be performed with IBM SPSS v. 24.

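### The gambling questionnaire (KFG) is described as a lifetime measure but analysed as an outcome at T2–T4, where it is insensitive to a reduction in gambling

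*Protocol article*

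**What the plan says.** The protocol article fixes four things that bear on this point.

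- **Recall frame.** Under Secondary Outcomes, Gambling, the KFG "addresses lifetime gambling behavior and consists of 20 items", each on a 4-point scale. "The threshold for pathological gambling is set at 16 points".
- **Schedule.** Table 3 ticks the KFG at T1, T2, T3 and T4. Assessment and Data Management places the first follow-up early: "post-intervention (T2) 7 weeks after randomization".
- **Purpose.** The Introduction says that "secondary outcome measures were chosen to assess a reduction in symptoms associated with IUD that were targeted in the intervention".
- **Analysis.** Statistical Methods plans "univariate analysis of covariance to compare secondary outcomes at post-treatment and 6- and 12-month follow-up adjusting for baseline scores". For every continuous measure it also computes Cohen's d by "standardizing the differences between baseline and follow-up scores by the pooled standard deviation of the baselines scores".

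The article gives no shorter window for the KFG at follow-up and does not exempt it from the outcome analysis. Where a measure is wanted only at baseline, Table 3 says so: RSES and Mini-SPIN are ticked at T1 alone.

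**The concern.** A lifetime score at T1 already contains all of the participant's gambling up to randomization. If the participant then gambles less, or stops, the correct lifetime answers do not change. The plan nevertheless treats the score as one that can show improvement over 7 weeks, 6 months and 12 months.

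What is at stake is interpretation. The Introduction names internet gambling among the forms of the disorder, so readers will look at this result. A null comparison could be reported as the intervention having no effect on gambling, when the instrument, as described, had little chance of showing one.

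**Working it through.** The plan states no figure here that could be reproduced. The check is one of logic, followed by an illustration and a count.

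**1. Within a participant.** Let L0 be the consistently answered lifetime score at T1 and Lt the score at a later visit, with higher values meaning more problematic gambling, as the 16-point threshold implies. The history up to the later visit includes the history up to T1, so Lt = L0 + I with I ≥ 0, where I is any increment from new or worse gambling since T1. Two things follow:
- The numerator of the planned baseline-to-follow-up Cohen's d cannot point towards improvement in either arm.
- A participant at or above 16 points at T1 cannot drop below that threshold later.

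**2. Between arms.** Randomization balances L0 in expectation, so the baseline-adjusted contrast estimates Δ = E[I, intervention] − E[I, control]. This need not be zero: it is negative if fewer intervention participants start or worsen. But a participant who improves contributes I = 0, however large the improvement. Because I ≥ 0, the benefit that can be seen is at most the mean rise in the control arm.

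**3. Illustration (all inputs assumed, none from the article).**
- Current severity at baseline: C0 ~ N(0, 1).
- Lifetime score at baseline: L0 = C0 + |N(0, 0.5)|, the second term being the excess of a past peak.
- Current severity at follow-up: C1 = C0 + δ + N(0, s), with δ = 0 in control and δ = −0.60 in intervention.
- Lifetime score at follow-up: L1 = max(L0, C1).
- 400,000 simulated participants per arm.

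| s | Mean change in L, control | Mean change in L, intervention | Difference in L | Difference in current severity |
|---|---|---|---|---|
| 0.3 | +0.033 | +0.000 | −0.033 | −0.600 |
| 0.6 | +0.112 | +0.018 | −0.094 | −0.601 |
| 1.0 | +0.245 | +0.094 | −0.151 | −0.600 |

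The lifetime score shows about 5% (0.033/0.600), 16% (0.094/0.601) and 25% (0.151/0.600) of the true effect. No simulated participant's lifetime score falls in either arm. The whole difference comes from control participants reaching new peaks more often.

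**4. Extent.** Besides the IAT, Table 3 measures 11 scales at T2, T3 and T4: CIUS, PHQ-9, GAD-7, AUDIT-C, ISI, PSWQ-3, GPS-K, KFG, WHO-5, AQoL-8D and WLQ. With one score per scale that is 11 × 3 = 33 comparisons, of which the KFG supplies 3. The article does not say that AQoL-8D and WLQ give one score each. If their eight and four dimensions were tested separately, the total would be (9 + 8 + 4) × 3 = 63, still with 3 from the KFG.

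**The case against.** The strongest reply is that everything rests on one word, *lifetime*, in a short description. The KFG items, response anchors and follow-up instructions are not shown, and an article may leave such instructions to the full protocol. Most of the other scales are also described without a recall window, so silence about a follow-up window is weak evidence. This stands as a limit on certainty. It does not remove the conflict: the article does not leave the frame open but states it, and that frame does not fit the stated schedule, purpose and analysis. If another window is used, the description is wrong and needs correcting.

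A reader might also infer that the KFG comparisons can show nothing, so that any difference must be recall error. The documents do not support that. The planned test compares arms, and step 2 above shows that arms can differ through fewer new or worsened cases.

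Nor does Statistical Methods itself give the KFG a direction; it speaks only of group differences. The aim of showing a reduction comes from the Introduction, where it concerns symptoms the intervention targets, and no core or elective session in Tables 1 and 2 is named for gambling. This weakens the expectation of an effect on gambling. It does not make a lifetime score suitable for detecting one, and the article still lists gambling among the secondary outcomes.

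**Conclusion.** The point holds in this form: followed as written, the plan uses a score that cannot register a reduction from baseline as an outcome meant to show one. The three KFG comparisons are insensitive to reduced gambling, and a null result would not be evidence of no effect.

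The conclusion assumes that *lifetime* describes the follow-up administrations as well as the baseline one, and that participants answer consistently. The 5% to 25% range depends on the assumed inputs and shows direction only; it is not an estimate for this trial.

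The problem is confined to one secondary scale. A reader might take it as a flaw in the trial's main result, but the primary IAT outcome and its analysis do not depend on the KFG. It should be put right, but it does not threaten the trial.

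**What to change.** Remove the KFG from the efficacy comparisons at T2, T3 and T4. Use the T1 score as a baseline descriptor and, within the exploratory regressions already planned, as a predictor. This follows the T1-only schedule that Table 3 gives RSES and Mini-SPIN. Report any KFG data collected at T2–T4 descriptively only, with a sentence saying that a lifetime score cannot show a reduction.

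If a current or since-last-assessment window is in fact used at follow-up, correct the Gambling section to say so, and do not apply the 16-point threshold to those scores.

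Do not change the follow-up instruction mid-trial without separating participants assessed under each version. Enrolment began on September 14th 2018 and the article describes the study as ongoing, so a new instruction could mix recall frames.

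The cost is one fewer secondary efficacy outcome, a wording change in the analysis plan and a registry note. If the KFG is also no longer given at follow-up, participants answer 20 fewer items at each of those visits.
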